### Observational study on the safety and potential efficacy of filtered sunlight phototherapy

A recent comprehensive systematic review of available evidence worldwide on PT found no randomized controlled trials (RCTs) dealing with either sunlight or environmental light
[26]. Prior to our proposed RCT to establish the effectiveness of FS-PT compared with CPT in a larger sample of infants, we conducted an observational study to evaluate safety and potential efficacy of two previously tested films for use in an inner-city maternity hospital in Lagos, Nigeria. FS-PT safety was determined through close monitoring of infant temperature, hydration status, and skin for signs of possible sunburn. Therapy was deemed safe on a given day if the infant did not have to be removed from phototherapy due to needing physician treatment for sunburn or dehydration, due to persistent temperature instability defined as two or more episodes of temperatures <35.0 or >39.0°C, or due to failure to return to normothermia (defined as 35.5 to 38.0°C) within 1 hour of being removed from FS-PT. Efficacy was evaluated by measuring the rate of rise/decline in total serum/plasma bilirubin (TSB) levels. Treatment was deemed safe and efficacious if the infant was able to stay in the FS-PT canopy for ≥5 hours per day and the rate of rise of TSB was <0.2 mg/dl/hour for infants ≤72 hours of age or if TSB decreased for infants >72 hours of age. This study was concluded in August 2012, details of which are scheduled for publication shortly. In summary, 203 term and near-term newborns (≤14 days old) with clinically significant jaundice as assessed by TSB levels were enrolled. They received treatment under a FS-PT canopy over a period of 227 days. Hourly measurements of axillary body temperatures and monitoring of sunburn, dehydration, and irradiances of FS-PT were performed. The results showed that FS-PT was efficacious in 94% (164/175) of the infants studied. Average irradiance from FS-PT was 37 ± 14 (range 8 to 65) μW/cm^2^/nm as measured by the Bili-Blanket Meter II^©^ (General Electric, Fairfield, CT, USA). No infant developed sunburn or dehydration, nor met exclusion criteria. Based on these favorable findings with our selected films (Gila Titanium and Air Blue 80 produced by CP Films Inc. Subsidiary of Eastman Chemical Co. Fieldale, VA, USA), we set out under the second phase of this project to demonstrate primarily in a RCT that FS-PT is just as efficacious as CPT in the treatment of infants with or at risk of severe NNJ.

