
## Methods/design

### Aims and hypotheses

The primary goal of this study is to demonstrate that the efficacy of FS-PT is no worse than that of CPT, with a non-inferiority margin of 10%. In effect, our null hypothesis is that this margin is above 10% suggesting that FS-PT is inferior to CPT.

The secondary goal of the study is to demonstrate that the proportion of infants who require exchange transfusion under FS-PT is no worse than that under CPT, with a non-inferiority margin of 5% based on a clinical rationale that FS-PT is non-inferior to CPT and still better than no treatment. This was also informed by the results of a meta-analysis of RCTs comparing CPT with no treatment which estimated that 10 infants needed to be treated with CPT to prevent an exchange transfusion
[26].

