#### Evaluation criteria

Change in TSB level per hour of therapy defined as a binary variable. The TSB level will be measured immediately before beginning therapy on a given day and immediately after therapy is completed that day, and the change in bilirubin level in mg/dl per hour of therapy will be calculated. For infants who are less than 72 hours old in the morning, the treatment will be judged efficacious if the bilirubin level rises more slowly than 0.2 mg/dl per hour of therapy that day. For infants who are more than 72 hours old, the treatment will be judged efficacious if the bilirubin level falls. Efficacy will be evaluated only for days in which the treatment was deemed safe (that is, when the infant did not have to be removed from PT due to a need for physician treatment for sunburn or dehydration, persistent temperature instability defined as two or more episodes of temperatures <35.0 or >39.0°C, or failure to return to normothermia (defined as 35.5 to 38.0°C) within 1 hour of being removed from PT). The average efficacy of each type of PT, defined as the proportion of safe days where a given therapy was used in which the therapy was efficacious, will be compared. FS-PT will be considered at least as efficacious as CPT if the average efficacy on days where FS-PT was used is no worse than 10% less than the average efficacy on days where CPT was used.

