### Sample size

The minimum sample size was estimated using the following assumptions: 1) the average efficacy of CPT is 80%; 2) the average efficacy of FS-PT is 80%; 3) there will be the same number of infants assigned to both groups; 4) the delta value is 10% - that is, we want to demonstrate that FS-PT is no more than 10% worse than CPT; and 5) 80% power, one-sided alpha = 0.025.

Under these assumptions, a total of 504 days, or 252 days in each treatment group, will be required. This calculation gives the required number of treatment days that are evaluable for efficacy. Since efficacy will be evaluated only for days in which the treatment was deemed safe, the sample size was increased to account for the possibility that the proportion of safe days might be as low as 90%. Assuming that the safety of both FS-PT and CPT is 90%, a sample size of 560 total days is required. Assuming that a typical course of treatment lasts 1 day, both for FS-PT and CPT, then 560 infants, or 280 infants in each group, will be required. Anticipating up to 10% loss due to rainy days (in the FS-PT group), delisting of infants by parents or guardians, or missing data (in both groups), we will enroll 616 infants, or 308 infants in each group. From our year 1 data in the preceding observational study only 66% of the 826 infants referred for elevated TcB had significant elevated TSB levels, hence 915 infants or more will be enrolled for stage 1 bilirubin estimation until the total requirement of 560 treatment days is reached (Figure 
2).

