### Data collection and analysis

Data will be collected on paper case report forms and entered via a web interface into a secure database. The study data will be collected and managed using REDCap (Research Electronic Data Capture) electronic data capture tools hosted at the University of Minnesota’s Academic Health Center. REDCap is a secure, web-based application designed to support data capture for research studies, providing: 1) an intuitive interface for validated data entry; 2) audit trails for tracking data manipulation and export procedures; 3) automated export procedures for seamless data downloads to common statistical packages; and 4) procedures for importing data from external sources.

Demographic data will be summarized and compared between the treatment and control groups using appropriate methods, such as Pearson’s chi-square test for categorical variables and two-sample t-tests for continuous variables. The primary objective is to compare the efficacy of FS-PT and CPT. A 95% exact binomial confidence interval for the true difference in efficacy between the FS-PT treated and CPT control groups will be calculated. FS-PT will be deemed non-inferior to CPT if the calculated confidence interval does not extend more than 10% below the equivalence point.

We plan to conduct three distinct analyses: an intent-to-treat analysis based on the assigned treatment for each enrolled infant, an as-treated analysis based on the actual treatment received on a given day and a per-protocol analysis including only enrolled infants who received the assigned treatment on all of their treatment days.

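### The evaluation criterion calls an FS-PT result up to 10 points below CPT 'at least as efficacious' and names no confidence interval, which conflicts with the interval rule for non-inferiority in the analysis section

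*Protocol article*

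**What the plan says.** The article states the primary conclusion in two places, and the two differ.

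- **Evaluation criteria (primary outcome).** Average efficacy is defined as the share of safe treatment days on which therapy worked, and the two averages are compared. The sentence with the conclusion opens "FS-PT will be considered at least as efficacious as CPT if the average efficacy on days where FS-PT was used"; the condition it then sets is a shortfall of at most 10 points against the CPT average. No interval is mentioned.
- **Data collection and analysis.** "A 95% exact binomial confidence interval for the true difference in efficacy between the FS-PT treated and CPT control groups will be calculated". The rule follows: "FS-PT will be deemed non-inferior to CPT if the calculated confidence interval does not extend more than 10% below the equivalence point".

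Two other places use the stronger kind of label. The section on the prior observational study says the second phase is meant to "demonstrate primarily in a RCT that FS-PT is just as efficacious as CPT". The Secondary outcome section uses the same label as the evaluation criterion when the exchange-transfusion proportion under FS-PT is at most 5 points higher than under CPT.

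Aims and hypotheses, by contrast, states the aim as showing that "the efficacy of FS-PT is no worse than that of CPT, with a non-inferiority margin of 10" per cent. The Sample size section uses the same margin with a one-sided alpha of 0.025.

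**The concern.** There are two faults in one sentence.

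The first is the label. A non-inferiority test with a 10-point margin can exclude a deficit larger than 10 points. It cannot show that the deficit is zero or less, which is what 'at least as efficacious' or 'just as efficacious' means. The same holds for the 5-point margin on exchange transfusion.

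The second is the rule. A limit of 10 points on the observed averages is not the same test as a limit of 10 points on the lower end of a 95% interval. The first takes no account of sampling error and does not hold the one-sided 2.5% error rate on which the sample size rests.

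Hospitals choosing between lamps and canopies would act on the stated conclusion. If the evaluation criterion were applied as written, a result whose interval shows FS-PT to be worse could be announced as at least as good.

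**Working it through.** **Inputs.** From Sample size: efficacy 80% in both arms, margin 10 points, 80% power, one-sided alpha 0.025, 252 evaluable days per arm. From the observational study: "FS-PT was efficacious in 94% (164/175) of the infants studied". All intervals below are Wald intervals on the difference (FS-PT minus CPT), an approximation to the exact interval the article names. Days are treated as independent.

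**1. The plan's own figure.** n per arm = (1.960 + 0.842)² × (0.8×0.2 + 0.8×0.2) / 0.10² = 7.849 × 0.32 / 0.01 = 251.2, rounded up to 252, or 504 in total. This matches, so the sample size belongs to the interval rule.

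**2. What each rule accepts with CPT at 80% and 252 days per arm.** For an observed deficit d, SE(d) = √{[0.8×0.2 + (0.8−d)(0.2+d)] / 252}.

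- Literal criterion: passes if d ≤ 10 points.
- Interval rule: passes if d + 1.96×SE < 10 points. At d = 2.84, SE is 3.65 and 2.84 + 7.16 = 10.0, so the largest passing deficit is about 2.8 points.
- Significantly worse: d > 1.96×SE. At d = 7.4, SE is 3.77 and 1.96×SE is 7.4, so this starts at about 7.4 points.

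Observed deficits of about 7.4 to 10 points therefore pass the literal criterion while being significantly worse. None of them passes the interval rule.

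**3. An example.** FS-PT 179/252 = 71.0%, CPT 202/252 = 80.2%. The difference is −9.1 points and SE = √[(0.7103×0.2897 + 0.8016×0.1984)/252] = 3.80 points. The 95% CI is −9.1 ± 7.5, that is −16.6 to −1.7. The literal criterion calls this at least as efficacious; the interval rule does not call it non-inferior.

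**4. Error rate at the margin (true 70% against 80%).** The SD of the difference is √[(0.7×0.3 + 0.8×0.2)/252] = 3.83 points.

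| Event | Normal approximation | Exact binomial enumeration |
|---|---|---|
| Literal criterion passes | Φ(0) = 50% | 51% |
| Literal criterion passes and CI excludes zero against FS-PT | Φ(0) − Φ((7.4−10)/3.83) = 0.50 − 0.25 = 25% | 25% |
| Interval rule passes | Φ(−1.96) = 2.5% | 2.5% |

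**5. Can the interval rule itself pass a significantly worse result?** The interval must lie wholly between −10 and 0, so its half-width must be below 5 points. At 80% and 252 days per arm the half-width is 1.96×√(0.32/252) = 7.0 points, so it cannot happen there. It can happen at higher success rates. With true FS-PT efficacy set at the pilot's 94% and CPT rates assumed, the share of trials that are both non-inferior and significantly worse is:

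| True CPT (assumed) | Share of trials |
|---|---|
| 94% | 2% |
| 95% | 6% |
| 96% | 15% |
| 97% | 32% |

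**The case against.** The strongest reply is that the analysis section already holds the right rule and the right label, and that the aims and the sample size agree with it. The 10-point limit also stands in the same sentence as the label, so a careful reader can see what the phrase is meant to cover. One may add that average efficacy in the evaluation criterion could mean the true rate, as it does in the sample size assumptions; the sentence would then state the hypothesis and leave the test to the analysis section.

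Part of this stands. A reader might infer that any result within 10 points below CPT would be reported as at least as efficacious, significantly worse results included. The documents do not support that, because the analysis section sets an interval rule that fails observed deficits beyond about 2.8 points at the planned size and 80% efficacy.

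A reader might also take large overlap figures as expected under the interval rule, such as 32% at CPT 97%. They need CPT rates that nothing in the article supports; its only CPT figure is the planning assumption that "the average efficacy of CPT is 80" per cent. The pilot's 94% is per infant, whereas the trial counts treatment days. An exact interval would generally be wider than the Wald interval and shrink the overlap. Some overlap is also a general property of precise non-inferiority trials, not a fault peculiar to this one.

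Finally, a reader might object that no superiority conclusion is provided for. The trial is framed and powered for non-inferiority, and such a step is commonly left to the statistical analysis plan, which is not shown. It is not a finding.

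What the reply does not remove is the conflict. The evaluation criterion defines average efficacy as the observed proportion of safe days, says that these are compared, and attaches a conclusion. Even on the kinder reading, the label claims more than a margin can support.

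**Conclusion.** The point holds as a conflict between two stated decision rules and as a label that is too strong. Taken literally, the evaluation criterion passes about 51% of trials at a true 10-point deficit (70% against 80%), where the design allows 2.5%. In about 25% of trials it would give that label to an FS-PT result whose 95% interval excludes zero in the wrong direction. These figures rest on 252 independent evaluable days per arm and Wald intervals.

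Under the interval rule in the analysis section, a result cannot be both non-inferior and significantly worse at about 80% efficacy. That becomes possible only at high success rates: about 2% of trials if both arms are at 94%, rising to 15% and 32% if CPT is assumed at 96% and 97%. The remedy is therefore in the wording of the rule and the conclusion. Sample size, margin and alpha are not in question here.

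**What to change.** 1. In the observational-study section, the Evaluation criteria and the Secondary outcome section, replace the 'at least as' and 'just as' efficacious labels with 'non-inferior to CPT within the stated margin' (10 points for efficacy, 5 points for exchange transfusion).
2. In the Evaluation criteria, replace the comparison of averages with the rule in Data collection and analysis: non-inferior if the lower limit of the 95% confidence interval for FS-PT minus CPT lies above −10 points.
3. State that an interval wholly between −10 and 0 is reported as non-inferior within the margin but less efficacious than CPT.

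The cost is wording only, with no change to sample size, data collection, margin or alpha. The downside is a less favourable claim in some outcomes.

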#### Treatment (stage 2)

FS-PT will be started in the morning after the irradiance level inside the canopy is at least 8 μW/cm^2^/nm, and will be stopped in the late afternoon when the irradiance level drops below 8 μW/cm^2^/nm or at any point during the day during a rainy/cloudy day when the irradiance stays below 8 μW/cm^2^/nm. If the irradiance persists below 8 μW/cm^2^/nm for more than 1 hour and the infant qualifies for PT per the AAP guideline, CPT will be initiated. If the irradiance again exceeds 8 μW/cm^2^/nm then the infant may again be placed in FS-PT.

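### The primary success rule sorts days by the therapy used, not by randomised arm, and the plan does not say which of its three analyses decides non-inferiority

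*Protocol article*

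**What the plan says.** All references are to the protocol article.

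- **Evaluation criteria (Primary outcome).** Average efficacy is "defined as the proportion of safe days where a given therapy was used in which the therapy was efficacious, will be compared". Success is judged on whether the "average efficacy on days where FS-PT was used is no worse than 10% less than the average efficacy on days where CPT was used".
- **Data collection and analysis.** A 95% exact binomial interval is planned for the "difference in efficacy between the FS-PT treated and CPT control groups", with one rule: the interval must not reach more than 10 points below equality. The next paragraph reads "We plan to conduct three distinct analyses: an intent-to-treat analysis based on the assigned treatment for each enrolled infant, an as-treated analysis" and adds a per-protocol analysis limited to infants who had their assigned treatment on every treatment day. The rule is not tied to any of the three.
- **Treatment (stage 2).** If canopy irradiance stays too low for more than an hour and "the infant qualifies for PT per the AAP guideline, CPT will be initiated". Prior and concomitant therapy and Pre-treatment (stage 1) also provide CPT for AAP-level infants when rain or cloud prevents FS-PT. No section moves a CPT infant to FS-PT.
- **Sample size.** The calculation assumes equal numbers of infants assigned to the two groups, a margin stated as "the delta value is 10% - that is, we want to demonstrate that FS-PT is no more than 10% worse than CPT", and "80% power, one-sided alpha = 0.025". Rainy days in the FS-PT group fall under an allowance for loss of up to 10%.

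**The concern.** Randomisation protects a comparison of infants as assigned. The stated success rule compares days as treated, and the route from one column to the other is selective. An FS-PT infant changes column only on a dull day and only if its bilirubin is at the AAP level. Enrolment starts 3 mg/dl below that level (Definition of high-risk threshold), so the infants who switch are the higher-bilirubin part of the FS-PT arm. Their whole switched days leave the FS-PT column and enter the CPT column. If they respond less well than average, FS-PT looks better and CPT looks worse.

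The protocol also treats such a day in four ways. The Evaluation criteria count it as a CPT day. Intent-to-treat counts it in the FS-PT arm. Per-protocol drops the infant. The sample size section treats rainy FS-PT days as lost.

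At stake is whether the primary claim rests on the randomised comparison, and which result decides if the three analyses disagree.

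**Working it through.** **1. The plan's own figure.** Inputs from Sample size: efficacy 80% in both groups, margin 10 points, one-sided alpha 0.025, power 80%.

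n per group = (1.960 + 0.842)² × (0.8×0.2 + 0.8×0.2) / 0.10² = 251.2, so 252 per group and 504 in total. Then 504 / 0.9 = 560, and 560 × 1.1 = 616. The stated figures reproduce. They describe one test between assigned groups.

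**2. Expected shift.** Let s be the share of FS-PT-arm days switched wholly to CPT, and g the number of points by which switched infants fall below average success. Both are assumptions; the documents give neither. CPT efficacy is 80%, and FS-PT is truly 10 points worse in every infant (at the margin).

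- Switched infants on CPT: 0.80 − g
- Non-switched infants on FS-PT: 0.70 + g·s/(1−s), which keeps the arm average at 0.70
- Intent-to-treat difference: −0.10 + 0.10·s
- Per-protocol difference: −0.10 + g·s/(1−s)
- As-treated difference: −0.10 + g·s/(1−s) + g·s/(1+s)

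For s = 10% and g = 20 points:

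- as-treated: −0.10 + 0.0222 + 0.0182 = −0.060
- per-protocol: −0.10 + 0.0222 = −0.078
- intent-to-treat: −0.10 + 0.010 = −0.090

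For s = 10% and g = −10 points (switched infants do better), as-treated is −0.10 − 0.0111 − 0.0091 = −0.120, which works against FS-PT.

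**3. Error rates.** Simulation with 252 days per arm, one day per infant, switched days drawn as Binomial(252, s), and a Wald 95% interval whose lower limit is compared with −10 points (1,000,000 trials per row). Nominal error is 2.5%.

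| Share switched | Switched infants' success on CPT | Intent-to-treat | As-treated | Per-protocol | Intent-to-treat and per-protocol both |
|---|---|---|---|---|---|
| 0% | – | 2.5% | 2.5% | 2.5% | 2.5% |
| 2% | 90% | 2.8% | 2.0% | 2.2% | 2.2% |
| 2% | 60% | 2.8% | 4.0% | 3.2% | 2.7% |
| 5% | 90% | 3.4% | 1.4% | 1.8% | 1.8% |
| 5% | 70% | 3.4% | 4.6% | 3.5% | 2.9% |
| 5% | 60% | 3.4% | 7.6% | 4.6% | 3.2% |
| 10% | 90% | 4.5% | 0.7% | 1.3% | 1.3% |
| 10% | 80% | 4.5% | 2.6% | 2.6% | 2.4% |
| 10% | 70% | 4.5% | 7.8% | 4.8% | 3.7% |
| 10% | 60% | 4.5% | 18% | 8.4% | 4.3% |

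Intent-to-treat exceeds 2.5% because switched infants received CPT and pull the arms together. It counts as error only if the target is the effect of FS-PT itself.

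**4. Multiplicity alone.** If the intent-to-treat difference is set at exactly −10 points, with 10% switched and average prognosis, letting any of the three analyses succeed gives 2.8% against 2.5%. The sorting of days matters more than the number of analyses.

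**5. Power of the paired rule.** With both therapies truly at 80% and switched infants of average prognosis, the same simulation gives 80.2% with no switching, 77.6% with 5% switched and 76.0% with 10% switched.

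**The case against.** **The analysis plan may settle it.** Ranking the three analyses is commonly left to the SAP, which is not shown. That is fair for the ranking taken alone. It does not cover the Evaluation criteria, where the protocol itself fixes success by therapy used. A SAP that put intent-to-treat first would contradict that text.

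**Stronger readings.** A reader might infer that success in any one of the three analyses is enough. The article does not say so; it only leaves open which one decides. A reader might also take the interval for the "difference in efficacy between the FS-PT treated and CPT control groups" as a second as-treated definition. It need not be: the same section calls the randomised arms the treatment and control groups, so those words can mean the arms as assigned.

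**The size is speculative.** This stands. The loss allowance of up to 10% pools rain with parental withdrawal and missing data. It is a ceiling on loss, not a count of switched days, and not every rained-off infant is at the AAP level. Nothing in the article shows that such infants meet the daily criterion less often, and if they meet it more often the rule is conservative. The 18% needs both the largest assumed share and a 20-point prognostic gap, so it should not be quoted as the expected effect.

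**The remedy is imperfect.** Also true. With average prognosis the as-treated rule holds its level while intent-to-treat is diluted. Per-protocol drops the same switched infants and is biased in the adverse cases. This is the reason to require two analyses to agree instead of relying on either alone.

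**Conclusion.** The point holds and should be fixed. As worded, the primary measure and its 10-point rule make a non-randomised comparison. They conflict with the protocol's own intent-to-treat analysis and with its sample-size basis. The article also leaves open which analysis its single non-inferiority rule governs.

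The direction and size of the bias cannot be determined from the documents. Under the assumptions shown, the as-treated error is 2.0–4.0%, 1.4–7.6% and 0.7–18% for switched shares of 2%, 5% and 10%. Intent-to-treat gives 2.8%, 3.4% and 4.5%. Requiring intent-to-treat and per-protocol together narrows the ranges to 2.2–2.7%, 1.8–3.2% and 1.3–4.3%. With no whole-day switching the three analyses coincide and nothing is inflated. These figures rest on one day per infant, a Wald interval in place of the planned exact one, and a true deficit of 10 points in every infant.

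**What to change.** - **Evaluation criteria:** in the definition ("defined as the proportion of safe days where a given therapy was used in which the therapy was efficacious, will be compared") and in the success rule ("average efficacy on days where FS-PT was used is no worse than 10% less than the average efficacy on days where CPT was used"), replace classification by therapy used with the treatment days of infants assigned to FS-PT and of infants assigned to CPT.
- **Data collection and analysis:** tie the confidence-interval rule to the assigned-arm (intent-to-treat) analysis. State that non-inferiority is claimed only if the per-protocol interval also stays above −10 points. Label the as-treated analysis descriptive.

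**Cost.** This changes wording in two sections, with no new data and no change to treatment rules. The stated 252 evaluable days per group can stay, and requiring two analyses to agree needs no split of alpha. The price is some power: in the setting above, from 80.2% to 77.6% or 76.0% if 5% or 10% of FS-PT days are switched. The paired rule reduces the inflation but does not fully remove it.
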